Because the most powerful studies are prospective studies, we chose a prospective parallel cohort design. We asked three primary care groups to invite their COPD patients for the e-Vita study. Because there are several differences between the groups (Fig. 3), we can not compare the COPD cohorts by combining data across three different groups. We chose for an interrupted time series (ITS) design to evaluate clinical outcomes (CCQ) within each group. In ITS studies, data are collected at multiple time points before and after an intervention in order to detect whether or not the intervention has a significantly greater effect than any underlying secular trend [26]. ITS can detect changes that are delayed or intermittent. It can also determine if the change is permanent or temporary. In addition, it allows evaluation of variables which are changing before the intervention, for instance, by comparing slopes of trend lines before and after the intervention. Finally, ITS makes it easier to control for confounding variables and regression to the mean [27]. The ITS will be performed according to guidelines of the EPOC Cochrane group [25]. Although well-conducted randomised trials provide the most reliable evidence on the effectiveness of interventions, they are not feasible for our setting of an implementation design with organisational changes in a real-life health care system within three different care groups with different demands. An advantage of an ITS design is that it allows for the statistical investigation of potential biases in the estimate of the effect of the intervention.

In addition to clinical outcomes, we also want to investigate the effect of different organisational implementation methods. Therefore we will implement the platform in group 1 and 2 using different methods. Differences will be measured using a parallel cohort design. To be certain that intervention groups will be balanced in known and unknown prognostic factors in the long run we will use randomisation within group 1 and 2. To rule out human influences we will randomise online for the level of support.

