**Fig. 2 Fig2:**
[figure not shown]
Research design for the different groups and interventions of e-Vita COPD

Organisational and technical differences are depicted in Fig. 2: three different care groups and two different web portals are included. Two different methods of implementation are distinguished within group 1 and 2: one with high level of personal assistance and one with low level of personal assistance. All patients in group 1 and 2 start with a personal instruction by the primary care nurse during a regular control visit. Patients will be randomly subdivided in two groups by computer by research assistants (randomisation is computerised to prevent human influence) with high (a) and low (b) level of support. In group 1a, high level support implies home visits for patients by a research nurse who accompanies the use of the web portal. In group 2a, high level support implies telephone consultation for patients by a research nurse who accompanies use of the web portal. In group 1b and 2b low level support implies that the primary care nurse shows the patient only once how to use the web portal (the usual organisational implementation method in daily practice) without any follow-up instruction. In group 3 the web portal is offered as free use: patients will receive instructions from the web portal itself. There will be no active support from caregivers or research nurses.

The groups differ in organisation, area, use of the web portal, and integration of the portal in a COPD disease management program (Fig. 3); these characteristics are based on Dutch reports of care groups [28]:

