Next, we will offer patients an online interactive care platform or web portal. The portal provides disease specific education and tips that fit their personal disease management program. In addition, the portal provides tools to report and monitor personal health goals, actions and health-related quality of life that can be shared with the patients’ own practice nurses. The portal in group 1 and 2 has better quality and more advanced possibilities for monitoring health goals with actions than the portal in group 3. The portal will be provided for a period of 15 months. Patients are informed by letter about the web portal. Patients in group 3 who agree to use the portal will receive instructions and log in information by e-mail. Patients in group 1 and 2 who agree to use the portal will be invited by their own practice nurses for intake. During intake the practice nurse defines a personal health goal together with the patient and gives instructions how and why to use the portal. Participants continue to receive regular COPD care by their GP and nurse practitioner according to the disease management program of the care group. Stable COPD patients visit their nurse practitioner yearly to check up on their disease management. The patient portal can be used by care professionals to prepare consultation or to monitor patients in-between their visits to their general practice.

Third, a subgroup of participants (1a and 2a) will receive extra support to use the portal by home visits or with instructions by telephone. During the home visit and consultation it will be checked if patients are able to log on the portal, if they understand the possibilities of the portal, and if they have started working on their personal health goal using the portal.

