### Data analysis

Along with our research design, analyses will be multilevel:To investigate the effect of the use of the web portal on the primary clinical outcomes, the ITS data will be analysed. The preferred method to analyse ITS studies is a statistical comparison of time trends before and after the intervention. Time series analysis using ARIMA models is one way of analysing the data, but there are a number of statistical techniques that can be used depending on the characteristics of the data, the number of data points available and whether autocorrelation is present. The final choice for the method to analyse the data will be made when the total set of data is available after consultation of a statistician.To investigate the effects of organisational aspects uptake of the portal will be analysed for care group 1, 2 and 3 using Chi Square tests (Fishers’ Exact Test for categorical variables and *F*-tests for continuous variables) and (repeated measures) ANOVA analyses. To analyse the effects of organizational aspects as described in the paper, the groups will be compared.To investigate the effect of integration of the web portal in daily practice, outcomes within integrated (group 1 and 2) and the free use groups (group 3) will be analysed using Chi Square tests (Fishers’ Exact Test for categorical variables and *F*-tests for continuous variables) and (repeated measures) ANOVA analyses.To investigate the effect of different organisational implementation methods, outcomes within groups with high level support (1a and 2a) and low level support (1b, 2b and 3) will be analysed using Chi Square tests (Fishers’ Exact Test for categorical variables and *F*-tests for continuous variables) and (repeated measures) ANOVA analyses.To explore correlation between self efficacy, sociodemographic characteristics on the one hand and adoption of the portal and clinical outcomes on the other hand, Pearson product-moment coefficients will be calculated across all research groups.To make a cost-effectiveness analysis, the direct costs of the different organisational implementation methods will be defined and analysed parallel to the effects of the portal in terms of Quality of Life (EQ-5D).

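### The high- versus low-support comparison counts the non-randomised group 3 as low support, so differences between care groups can appear as an effect of support

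*Protocol article*

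**What the plan says.** Methods/Design states the scope of randomisation: "we will use randomisation within group 1 and 2", and "we will randomise online for the level of support". The text under Fig. 2 describes the arms. High support is home visits in 1a and telephone consultation in 2a. For the other two randomised arms, "In group 1b and 2b low level support implies that the primary care nurse shows the patient only once how to use the web portal". Group 3 is described on its own: "There will be no active support from caregivers or research nurses".

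Group 3 differs in other ways too. The text under Fig. 3 says that its portal is not integrated in the disease management programme. The Intervention section says that its caregivers receive no training, whereas those in groups 1 and 2 do, and that "The portal in group 1 and 2 has better quality and more advanced possibilities" than the portal in group 3.

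For the effect of implementation method, the Data analysis section states that "outcomes within groups with high level support (1a and 2a) and low level support (1b, 2b and 3) will be analysed", using chi-square or Fisher tests, F-tests and (repeated measures) ANOVA. For the effect of integration, it states that "outcomes within integrated (group 1 and 2) and the free use groups (group 3) will be analysed" with the same tests. It mentions no stratification or adjustment by care group for either.

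**The concern.** Support level is the one factor in this study that is randomised, and the article says randomisation is there to balance known and unknown prognostic factors. Adding a whole non-randomised care group to one side weakens that balance. A difference between the two sides could come from group 3's portal, its lack of integration, its untrained caregivers or its patient population, and still be reported as an effect of personal support.

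The article's own hypotheses suggest a direction. The Abstract expects integration in a care programme to increase use and health status, and the Discussion expects well-organised care groups with skilled staff to show more portal use and better health status. If so, group 3 would do worse for reasons other than support, and the contrast would favour high support even if support did nothing. This applies to portal use as well as to CCQ.

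**Working it through.** **1. The plan's own sample size.** The Power calculation section gives a difference of 0.5 CCQ points, SD 0.75, α = 0.05, 80% power and 37 patients. The normal formula for two means, two-sided, is n = 2 × [0.75 × (1.960 + 0.842) / 0.5]² = 35.3 per arm. The two-sample t-test version gives 36.3, rounded up to 37. So 37 is reproduced as a per-arm number for a two-arm comparison.

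**2. Planned arm sizes.** The article plans 45 per implementation method: 2 × 45 = 90 in group 1, 90 in group 2 and 45 in group 3, in total 225. I use 45 as stated.
- High support (1a + 2a): 45 + 45 = 90.
- Low support as planned (1b + 2b + 3): 45 + 45 + 45 = 135, of which group 3 is 45/135 = 33%.
- After the stated 20% drop-out: 72 versus 108, or 72 versus 72 without group 3.

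**3. Bias.** Let D be the difference in mean CCQ between group 3 and arms 1b/2b that is not due to support. The documents do not give D. With no true support effect, the contrast is expected to be D × 45/135 = D/3.

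**4. False-positive rate (illustration).** This is a comparison of levels at one time point, with SD 0.75 on both sides.

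SE = 0.75 × √(1/72 + 1/108) = 0.114.

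Rate = Φ(bias/SE − 1.96) + Φ(−bias/SE − 1.96).

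| Assumed D | Bias D/3 | Rate, 72 vs 108 |
|---|---|---|
| 0 | 0 | 5% |
| 0.2 | 0.07 | 9% |
| 0.3 | 0.10 | 14% |
| 0.5 | 0.17 | 31% |

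Without drop-out (90 versus 135, SE 0.102), D = 0.2, 0.3 and 0.5 give about 10%, 17% and 37%.

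**5. Cost of leaving group 3 out.** With 72 versus 72, SE = 0.75 × √(2/72) = 0.125. Stratifying by care group gives the same value: each stratum has 36 versus 36, SE = 0.75 × √(2/36) = 0.177, and the average of two such estimates has SE 0.177/√2 = 0.125.

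| After drop-out | SE | Power for 0.5 points, Φ(0.5/SE − 1.96) | Detectable difference at 80% power, 2.80 × SE |
|---|---|---|---|
| As planned, 72 vs 108 | 0.114 | 99.2% | 0.32 |
| Randomised arms only, 72 vs 72 | 0.125 | 97.9% | 0.35 |

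**6. Integration contrast.** Here 90 + 90 = 180 patients in groups 1 and 2 face 45 in group 3. Integration coincides exactly with care group, portal and caregiver training, so the full difference between care groups enters the contrast, not a third of it. In addition, 90 of the 180 receive high support and none of the 45 do. No randomised subset addresses integration.

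**The case against.** The strongest defence is that this is an additional aim. The primary analysis is the ITS within each care group, which is unaffected. Two thirds of the low-support side (90 of 135) is randomised, and 1a versus 1b and 2a versus 2b can always be computed from the same data. All of that stands.

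A condensed article might also leave unsaid that care group enters the ANOVA as a factor. That is possible, but it does not rescue the wording. Group 3 contains no high-support patients, so with care group as a factor it would carry no information on the support effect. Listing it under low support is then either idle or confounding.

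A reader might infer several stronger things that the documents do not support:
- **That the analysis breaks the article's own ban on combining groups.** The sentence "we can not compare the COPD cohorts by combining data across three different groups" leads into the choice of ITS within each group and serves to justify that choice. Its reason, that the groups differ, applies here too, but it is not a rule written for this comparison.
- **That group 3 fails the article's definition of low support.** The single nurse demonstration is stated for 1b and 2b only; there is no general definition. The article merges two different kinds of low support.
- **That an error rate of 14% to 31% has been established.** D is assumed, and at D = 0 there is no inflation. The article also names repeated-measures ANOVA; in a group-by-time test, stable level differences cancel and only differential change would bias the result.
- **That the integration comparison has the same flaw.** It was never randomised, so no protection is lost, and the article describes the group differences openly. The fault there lies in calling the result an effect of integration.

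**Conclusion.** The point holds for the support contrast as stated in the Data analysis section. One third of the low-support side comes from a care group that was not randomised and that differs in portal, integration, caregiver training and instruction, and no adjustment is stated. The structural result, a bias of D/3, needs only the planned arm sizes. The error rates need more: an assumed D, a single-time-point comparison of levels and SD 0.75. They show the possible scale and are not a forecast. Randomisation is diluted rather than lost, and the primary ITS result is not in question.

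The integration contrast is a separate matter. It is confounded by design, restriction cannot remove the confounding, and what can be corrected is the choice of comparator and the label.

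**What to change.** - **Support effect.** Define it as 1a versus 1b and 2a versus 2b, combined with care group as a stratum. Stratifying also respects the fact that high support takes a different form in 1a and 2a. Report group 3 separately.
- **Integration.** Compare 1b + 2b with group 3, which removes the imbalance in high support (planned 90 versus 45). Call it a descriptive comparison of packages that differ in care group, portal, training and instruction as well as integration.

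Both are changes of analysis wording, with no change to recruitment or data collection. The support comparator falls from 135 to 90 planned patients, which costs about one percentage point of power for 0.5 points and moves the detectable difference after drop-out from 0.32 to 0.35. The choice of statistical model within this frame can stay with the analysis plan.

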##### Adoption of the portal

Usage of the portal is monitored continuously by log files. User satisfaction is measured by purpose-designed questionnaires.

From the organisational perspective we will measure the following outcome:

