#### Determinants

##### Self-efficacy

Self-efficacy is measured using the Generalized Self-Efficacy Scale (GSES), which will be displayed at baseline. This 10-item questionnaire was designed in 1981 by Schwarzer [35]. The items are scored on a four-point scale, in which a higher score reflects higher self-efficacy. Research in 28 countries showed that Cronbach’s alpha varies between .76 and .90, of which mostly above .80. Self-efficacy is derived from the Social Cognitive Theory, which states that behavioral change is made possible by personal sense of control. Self-efficacy is the “belief in one’s capabilities to organise and execute the courses of action required to produce given attainments”. Research shows that self-efficacy is an important factor for self-management in behavioral change of the chronic ill, such as diabetics and cardiovascular patients. For example, in people with type 2 diabetes self-efficacy is an important factor influencing self-management behaviours; self-efficacy impacts adherence to treatment [36].

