##### Sociodemographic characteristics

These are assessed by a purpose-designed online questionnaire. We include the following characteristics: age, socioeconomic status, marital status, and general use of online and digital products and services. Since decreased access to internet and decreased general health outcomes have been associated with lower socioeconomic status, minority racial/ethnic groups, older age, and poorer health we will include these characteristics in our study.

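### Pearson coefficients pooled over all care groups do not suit unordered determinants and can reflect care-group differences

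*Protocol article*

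**What the plan says.** The Data analysis section of the protocol article gives the purpose as "To explore correlation between self efficacy, sociodemographic characteristics on the one hand and adoption of the portal and clinical outcomes on the other hand", and the method in the same sentence: "Pearson product-moment coefficients will be calculated across all research groups". It states no stratification, no adjustment for care group and no other coefficient for other types of variable.

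The variables are described elsewhere:

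- **Sociodemographic characteristics:** the section lists "age, socioeconomic status, marital status, and general use of online and digital products and services". Its next sentence, on "lower socioeconomic status, minority racial/ethnic groups, older age, and poorer health we will include these characteristics in our study", adds race or ethnicity.
- **Self-efficacy:** a 10-item scale. "The items are scored on a four-point scale, in which a higher score reflects higher self-efficacy".
- **Adoption of the portal:** "Usage of the portal is monitored continuously by log files". Satisfaction questionnaires are added. No usage metric is defined.

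On the care groups, Methods/Design says that they differ in organisation, area, portal use and integration. The Intervention section gives caregivers training in groups 1 and 2 and none in group 3, and says: "The portal in group 1 and 2 has better quality and more advanced possibilities". Methods/Design and the Discussion expect use to rise with personal support, and Methods/Design also with integration into an existing care programme.

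**The concern.** Two features of the fixed method cause trouble.

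**Variable type.** Pearson's r treats the numeric codes of a variable as distances. An unordered variable with more than two categories has no such distances, so the coefficient measures the coding as much as the data.

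**Pooling.** Care group is expected to influence portal use, and it may also go with age, socioeconomic status or self-efficacy, because the groups come from different areas and organisations. A coefficient over all patients then mixes the association between groups with the association inside them. It can show a relation that exists in no group, or hide one that exists in each.

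This is the only stated analysis that links patient-level determinants to adoption and clinical outcome. Read as written, it could name a determinant that is really a marker of care group or of a coding choice.

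**Working it through.** The article gives no figure for this analysis, so there is none to reproduce. The only document inputs are the planned group sizes in the Power calculation section, 90 + 90 + 45 = 225. All shifts, shares and means below are assumptions for illustration.

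**1. Pooling.** Let group 3 be a share p = 45/225 = 0.20 of the patients, so p(1-p) = 0.16. Let it differ from groups 1 and 2 by dx SD on the determinant and dy SD on the outcome, with within-group SD 1 and no correlation inside any group. The pooled coefficient is

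r = p(1-p)·dx·dy / sqrt[(1 + p(1-p)·dx²)(1 + p(1-p)·dy²)]

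| dx / dy (SD) | Calculation | Pooled r | Within-group r |
|---|---|---|---|
| 0.5 / 0.5 | 0.04 / 1.04 | 0.04 | 0 |
| 1 / 0.5 | 0.08 / sqrt(1.16 × 1.04) | 0.07 | 0 |
| 1 / 1 | 0.16 / 1.16 | 0.14 | 0 |
| 1.5 / 1 | 0.24 / sqrt(1.36 × 1.16) | 0.19 | 0 |

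If instead all three groups differ by a step of d SD on both variables (means 0, d, 2d; weights 0.4, 0.4, 0.2), the between-group variance is (1.2 - 0.64)d² = 0.56d², and r = 0.56d² / (1 + 0.56d²). Steps of 0.5, 0.75 and 1 SD give 0.12, 0.24 and 0.36.

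The artefact is therefore small for modest differences and becomes material only when the groups differ clearly on both variables.

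**2. Coding of an unordered variable.** Assume four categories A to D with shares 60, 15, 10 and 15%, outcome means 0, 0.5, 0 and 0.5 SD, and within-category SD 1.

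- Overall mean: 0.30 × 0.5 = 0.15.
- Between-category variance: 0.30 × 0.25 - 0.15² = 0.0525.
- Correlation ratio, which does not depend on codes: sqrt(0.0525 / 1.0525) = 0.22.
- Codes A=1, C=2, B=3, D=4: covariance 0.525 - 1.85 × 0.15 = 0.2475, code variance 4.75 - 1.85² = 1.3275, so r = 0.2475 / sqrt(1.3275 × 1.0525) = +0.21.
- The same codes reversed: r = -0.21.
- Codes B=1, A=2, C=3, D=4: covariance 0.375 - 2.25 × 0.15 = 0.0375, code variance 5.85 - 2.25² = 0.7875, so r = 0.0375 / sqrt(0.7875 × 1.0525) = +0.04.

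Over all 24 codings r runs from -0.21 to +0.21, with identical data throughout.

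**3. Where Pearson is acceptable.** The self-efficacy score is a 10-item total and approximately continuous, age is continuous, and a two-category variable has only one contrast. For these the coding problem does not arise, though the pooling problem still does.

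**The case against.** The strongest case against the point is that this is an exploratory secondary analysis on which no primary conclusion, power figure or randomised comparison depends. The article does not say how marital status is coded. A partner/no-partner split would remove the coding problem for it, and an article commonly leaves such detail to the full protocol. The care groups share eligibility criteria, so a gap of 1 SD in a patient characteristic may be unrealistic, and at 0.5/0.5 SD the artefact is only about 0.04. All of this stands and limits the size of the point. It does not remove it, because the article fixes the coefficient and the pooling positively and leaves neither open.

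A reader might infer four stronger things, which the article does not support:

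- **That the article contradicts its own ban on pooling.** Methods/Design says "we can not compare the COPD cohorts by combining data across three different groups", but this concerns comparing the cohorts and leads to the choice of interrupted time series within each group. It does not forbid every association across patients. The reason given, that the groups differ, is still relevant here.
- **That usage is a skewed count with many zeros.** The metric is not defined, so this is a guess. Skewed usage would make r sensitive to heavy users but not meaningless.
- **That false significant findings will follow.** The article says the coefficients will be calculated in order to explore. It states no test or threshold for them.
- **That this is the only analysis of adoption.** Uptake is also compared between care groups, and outcomes by integration and by support level. The correlations are the only analysis of patient-level determinants.

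The wording on all research groups could also mean one coefficient per group. The plain reading is a pooled one, and if the other is meant, the text should say so.

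**Conclusion.** The point holds as a modest one. Pearson's r is the wrong measure for any unordered determinant with three or more categories: racial or ethnic group, and marital status if so coded. For every determinant, pooling without care group lets differences between groups enter the coefficient. With no relation inside the groups and only group 3 shifted, the pooled r is about 0.04 at 0.5/0.5 SD, 0.14 at 1/1 SD and 0.19 at 1.5/1 SD. Which of these applies is unknown, since the article gives no figures on how the groups differ in these characteristics. The conclusion rests on the plain reading that the coefficients are pooled and unadjusted.

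**What to change.** Estimate these associations within each care group, or in a regression with care group as a fixed effect. A term for support arm is optional: support level is randomised within groups 1 and 2, so there it would serve precision and not control of confounding. Enter nominal variables as indicator terms. Keep Pearson's coefficient, within group, for the self-efficacy score, age and two-category variables if a simple correlation is wanted. Define the usage metric, and use a rank-based coefficient or a model suited to that metric if usage proves skewed.

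The cost is a change of wording in the analysis section and a few degrees of freedom. No additional data are needed, because care group and support arm are known for every patient and the determinants are already planned for collection.
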